### Treatment Integrity

Throughout the delivery of the intervention, several aspects were considered to assure that treatment integrity was maintained. All therapists had a minimum MSc degree in Clinical Psychology and were certified therapists with clinical experience in ACT and compassion-based interventions. A manual for the intervention therapists was developed, and all therapists were trained in delivering the intervention.

### Primary and Secondary Outcomes in the RCT

Participants completed self-report measures at four different times: baseline (T0), follow-up (T1), and 3-month (T2), and 12-month (T3) follow-ups (Table 2). Participants additionally provided blood and stool samples at T0 and T3. Mayo Scores or Harvey-Bradshaw Scores were assessed at T0 and T2.

**Table 2 T2:** Schedule of enrollment, intervention, and assessments.

	**Study Period**					
	**Enrollment**	**Allocation**	**Post-allocation**			
**Timepoint**	–t2	–t1	t0	t1	t2	t3
**Enrollment**						
Informed consent	x					
Eligibility screen	x					
Blinded randomization		x				
Allocation		x				
**Intervention**						
LIFEwithIBD						
Waiting list						
**Primary outcome**						
DASS-21			x	x	x	x
**Key mediators**						
SELFCS			x	x	x	x
CompACT			x	x	x	x
**Secondary outcomes**						
WSAS			x	x	x	x
EUROHIS-QOL-8			x	x	x	x
IBDQ-UK			x	x	x	x
CISS			x	x	x	x
IBD symptom perception			x	x	x	x
Mayo score			x		x	
Harvey-Bradshaw score			x		x	
C-Reactive protein			x			x
Hemogram			x			x
Albumin			x			x
Fecal calprotectin			x			x
Gut microbiota			x			x
Acceptability questions^a^				x		

a *only for the experimental condition*.

*DASS-21, Depression Anxiety Stress Scales; SCS, Self-Compassion Scale; CompACT, Comprehensive assessment of Acceptance and Commitment Therapy processes; WSAS, Work and Social Adjustment Scale; EUROHIS-QOL-8, EUROHIS-QOL 8-item index; IBDQ-UK, Inflammatory Bowel Disease Questionnaire–UK version; CISS, Chronic Illness-related Shame Scale; IBD Symptom Perception, measured by the IBD symptoms scale*.

#### Primary Outcome

##### Psychological distress

This outcome was assessed by the *Depression Anxiety Stress Scales* (DASS-21) (64, 65), a well-known 21-item measure of depressive (e.g., “I felt I wasn't worth much as a person”), anxiety (e.g., “I felt scared without any good reason”), and stress (e.g., “I found it hard to wind down”) symptoms during the precedent week, using a 4-point scale [ranging from “*did not apply to me at all” (0)* to “*applied to me very much, or most of the time” (3)*]. Higher scores indicate higher psychological distress. The DASS-21 presented good internal consistencies for all subscales both in original (α_depression_ = 0.88; α_anxiety_ = 0.82; α_stress_ = 0.90) and in the Portuguese psychometric validation studies (α_depression_ = 0.85; α_anxiety_ = 0.74; α_stress_ = 0.81).

#### Key Mediators

##### Self-compassion

Self-compassion was measured by the *Self-Compassion Scale* (SCS) (66, 67), a widely used 26-item measure that takes into consideration respondents' perceived actions toward themselves during difficult situations. Each item is rated on a 5-point Likert scale [from “*Almost never” (1)* to “*Almost always” (5)*]. The SCS can be divided into two global dimensions (67, 68): (i) compassionate self-responding: this dimension comprises the “self-kindness” (e.g., “I am kind to myself when I am experiencing suffering”), “common humanity” (e.g., “When I feel inadequate in some way, I try to remind myself that feelings of inadequacy are shared by most people'), and “mindfulness” (e.g., “When I fail at something important to me I try to keep things in perspective”) subscales; (ii) uncompassionate self-responding: comprises the “self-judgement” (e.g., “I am intolerant and impatient toward those aspects of my personality I don't like”), “isolation” (e.g., “When I fail at something that's important to me, I tend to feel alone in my failure”), and “overidentification” (e.g., “When I fail at something important to me, I become consumed by feelings of inadequacy”) subscales. The internal consistency for the SCS was found to be excellent (α = 0.92) in the original study and good in the Portuguese validation study (α = 0.89).

##### Psychological flexibility

Psychological flexibility variable was measured by the *Comprehensive assessment of Acceptance and Commitment Therapy processes* (CompACT) (69, 70), a general self-report measure of the ACT processes which, in its Portuguese version, is composed of 18 items with three dimensions of psychological flexibility: (i) openness to experience (e.g., “I try to stay busy to keep thoughts or feelings from coming”–reverse item), behavioral awareness (e.g., “It seems I am ‘running on automatic' without much awareness of what I'm doing”–reverse item), and valued action (e.g., “I behave in line with my personal values”). Each item is rated on a 7-point scale [from “*Never true” (0)* to “*Always true” (6)*]. Higher scores indicate greater psychological flexibility. In the original study (69), the CompACT presented good internal consistencies (with Cronbach's alphas varying between 0.87 and 0.91). The CompACT's Portuguese 18-item version showed acceptable to good internal consistencies with Cronbach's alphas between 0.77 and 0.88 (70). Also, the CompACT's 18-item was used in another Portuguese study presenting a Cronbach's alpha of 0.84 for the total scale and between 0.76 and 0.88 for the subscales (71).

#### Secondary Outcomes

##### Functional impairment

This outcome was measured by the *Work and Social Adjustment Scale* (WSAS) (72), a 5-item measure of perceived functional impairment in daily activities, such as work, family, interpersonal relations, social and private leisure activities, and home management. Each item is rated on a 9-point scale [“*Not at all” (0)* to “*Very severely” (8)*]. Higher scores denote higher functional impairment. The original study showed good internal consistencies throughout several different conditions (ranging between 0.70 and 0.94). The WSAS's psychometric properties, validity and sensitivity to change have been demonstrated by a wide range of studies (73). In a Portuguese study, the WSAS has shown a good internal consistency (α = 0.87) (55).

##### General quality of life

This outcome was evaluated by the *EUROHIS-QOL 8-item index* (74–76), a quality of life measure composed of eight items (regarding general health, energy, daily living activity, overall quality of life, finances, social relationships, self-esteem, and home) which were extracted from the WHOQOL-Bref. Each item has an individualized 5-point Likert scale (the same response scales used in the WHOQOL-bref). Higher scores indicate higher quality of life. The EUROHIS-QOL 8-item index showed good discriminant validity, and it is considered a useful instrument to evaluate treatment effectiveness (77). The initial study was conducted in 10 countries and revealed an overall Cronbach's alpha of 0.83 (75). Similarly, the Portuguese validation study also showed a good internal consistency (α = 0.83) (76).

##### Health-Related quality of life

This outcome was measured by the *Inflammatory Bowel Disease Questionnaire–UK version* (IBDQ-UK) (78), which is the Anglicized 30-item version of the IBDQ (79, 80), an IBD-specific quality of life instrument. The IBDQ-UK's authors have modified the wording of some questions and simplified their response options. Each item is rated on a 4-point scale (three questions have an additional “non-applicable” option available) ranging from “*no, no at all/none” (0)* to “*on 8 to 14 days (i.e., more than every other day)/Yes, all of the time” (4)*. Participants are asked to answer questions regarding their IBD and how it has affected their lives during the previous 2 weeks. The internal consistency for the IBDQ-UK in its original study was found to be excellent (Cronbach's alpha of 0.94).

##### Chronic illness-related shame

Illness shame was assessed by the *Chronic Illness-related Shame Scale* (CISS) (81), a 7-item unidimensional scale that was specifically designed to evaluate shame associated with the experience of having a chronic illness and/or its related symptoms (e.g., “I feel inadequate because of my illness and symptoms,” “I'm ashamed of talking with others about my illness or symptoms,” “I feel that my illness is embarrassing”). Each item is rated on a 5-point Likert scale [from “*Never true” (0)* to “*Always true” (4)*]. Higher scores reflect higher levels of chronic illness shame. The original study was conducted in Portugal, in which the CISS revealed a very good internal consistency (α = 0.91).

##### IBD symptom perception

Symptom perception was measured by the *IBD symptoms scale* (15), a 16-item self-report Portuguese scale which was developed to evaluate the frequency of IBD symptoms during the precedent month (e.g., fatigue, abdominal pain and bloating, flatulence, diarrhea, nausea or vomiting, fever, the urgency to evacuate). Each item is rated on a 7-point scale [ranging from “*Never” (0)* to “*Always” (6)*]. Higher scores indicate a higher level of IBD symptom perception.

##### Disease activity

The Mayo Score (non-invasive 9-point partial Mayo Score; for ulcerative colitis participants) (82) and Harvey-Bradshaw Score (83) (for Crohn's Disease participants) were analyzed considering assessments by participants and their physician. The physician was blinded to participants' allocation. These scores indicate IBD activity. The partial Mayo score refers to stool frequency, rectal bleeding, and the physician's global assessment; the Harvey Bradshaw Score assesses general well-being, abdominal pain, number of liquid/sift stools, abdominal mass, and presence of extra-intestinal manifestations.

##### Biomarkers

An erythrogram, leukogram, and thrombogram were obtained from all participants since hematological alterations such as anemia, thrombocytosis and leukocytosis, may be observed in some patients, in particular during flares. C Reactive Protein (CRP) was also determined (by immunoturbidimetry) since it is an acute-phase reactant and therefore is a reliable biomarker to assess inflammatory states. Hence, although not specific for IBD, CRP is regularly monitored in patients in order to assess the degree of intestinal inflammation. Finally, serum albumin was determined (by colorimetry) since it tends to decrease rather quickly in severely ill patients. In fact, hypoalbuminemia is frequently observed in patients with uncontrolled disease or with prolonged and frequent flares (84). The blood specimens were analyzed according to the Coulter principle (impedance).

In order to assess a specific biomarker, intestinal inflammation was investigated by quantifying fecal calprotectin. Indeed, fecal calprotectin is a valuable and sensible tool to monitor IBD progression and anticipate relapses, correlating well with the degree of endoscopic and histological inflammation (85). Fecal calprotectin was determined using Buhlmann's Quantum Blue® fcal assay. Briefly, calprotectin was extracted from stools using a Calex® cap pre-filled with extraction buffer and applied to a lateral flow test cassette adsorbed with a monoclonal antibody against human calprotectin. The cassette was then inserted into Buhlmann Quantum Blue® reader which immediately started the reading process, converting the image analysis into a quantitative result (μg/g).

Gut microbiome was sequenced in the stools of patients before and after the psychological intervention in an attempt to establish a mechanist link between bacteria richness and diversity with disease progression (in terms of clinical and psychological outcomes) and biochemical indicators.

### Acceptability Assessment

Participants in the experimental condition answered a questionnaire regarding the quality of the LIFEwithIBD intervention, the provided resources (audio files, participants manual), and participants' perceived change (e.g., IBD symptoms, ability to self-regulate emotions, quality of life, perception of change by closed ones). The intervention's attrition will also be considered a measure of acceptability.

### Data Analysis

All analyses are planned as intent-to-treat (ITT). The primary outcome will be the psychological distress (DASS-21–*depression, anxiety, and stress*) measured at 8 weeks (immediately post-intervention) between the two intervention groups and adjusting for baseline scores using ANCOVA. We will examine the ANCOVA's assumptions through standard tests and residual plots and perform transformations. The magnitude of the differences between-treatment groups will be expressed as the standardized mean difference.

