## Abstract

**Background:** There is ample evidence of the high mental health burden caused by Inflammatory Bowel Disease (IBD). Several constructs such as experiential avoidance, cognitive fusion, shame, and self-criticism have recently emerged as potential intervention targets to improve mental health in IBD. Psychotherapeutic models such as Acceptance and Commitment Therapy and compassion-based interventions are known to target these constructs. In this protocol, we aim to describe a two-arm Randomized Controlled Trial (RCT) testing the efficacy of an ACT and compassion-focused intervention named Living with Intention, Fullness, and Engagement with Inflammatory Bowel Disease (LIFEwithIBD) intervention + Treatment As Usual (TAU) vs. TAU in improving psychological distress, quality of life, work and social functioning, IBD symptom perception, illness-related shame, psychological flexibility, self-compassion, disease activity, inflammation biomarkers, and gut microbiota diversity.

**Methods:** This trial is registered at ClinicalTrials.gov (Identifier: NCT03840707, date assigned 13/02/2019). The LIFEwithIBD intervention is an adaptation to the IBD population of the Mind programme for people with cancer, an acceptance, mindfulness, and compassion-based intervention designed to be delivered in a group format. The LIFEwithIBD intervention's structure and topics are presented in this protocol. Participants were recruited at the Gastroenterology Service of the Coimbra University Hospital between June and September 2019. Of the 355 patients screened, 61 participants were selected, randomly assigned to one of two conditions [experimental group (LIFEwithIBD + TAU) or control group (TAU)] and completed the baseline assessment. Outcome measurement took place at baseline, post-intervention, 3- and 12-month follow-ups.

**Discussion:** Results from this RCT will support future studies testing the LIFEwithIBD intervention or other acceptance and/or compassion-based interventions for IBD.

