### Randomization of Participants

Figure 1 shows the flow of participants through the study. Of the 355 patients screened, 279 were excluded for not meeting criteria to participate. Seventy-six participants were randomly assigned to one of two conditions: experimental group (Treatment as Usual + LIFEwithIBD intervention: *n* = 38) or control group (TAU: *n* = 38), through computed-based randomization (www.random.org/lists/). Before the start of the intervention, all participants were contacted by phone. In this process, 6 patients self-excluded from the study due to a lack of resources to attend the sessions (e.g., lack of time, transportation).

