## Discussion

Among those designed for or tested in IBD, the LIFEwithIBD intervention is the first to integrate ACT and compassion approaches. The RCT presented in this protocol paper will provide evidence on the efficacy of this intervention (which was delivered along with TAU) in improving health outcomes in comparison to the exclusive delivery of TAU (medical treatment). Due to the inactive nature of the control condition, future studies should compare the intervention's efficacy to other conditions such as active controls (e.g., psychoeducation) and other psychological interventions tested in IBD, such as Cognitive and Behavioral Therapy (86) or Hypnotherapy (87). The use of an inactive control will indeed be a significant limitation to this RCT, especially considering that participants allocated to this condition were aware of their non-allocation to the intervention group, which may influence answers to the administered self-report questionnaires. Also, contact with a group of people with the same pathology, as well as with the therapists, may in itself provide therapeutic effects only experienced by the experimental group, which adds to the disparity between the study groups. Nevertheless, considering this is the first time the LIFEwithIBD intervention will be tested, the use of an inactive control may provide useful preliminary results on the effects of the intervention.

The greatest limitation to this RCT appears to be participant retention, similarly to previous RCTs testing group interventions in this population, which also showed large attrition rates (25, 86). In the current study this may have been due to participants not being compensated for their participation besides receiving the intervention. Results from this RCT will act as support for future studies testing the LIFEwithIBD intervention or other acceptance and/or compassion-based interventions for IBD.

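### The article gives both 76 and 61 as the number randomised, so the intent-to-treat set is unclear and, if it is the 61 with a baseline, wrongly labelled

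*Protocol article*

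**What the plan says.** **Number randomised.** Randomization of Participants reports "Of the 355 patients screened, 279 were excluded for not meeting criteria to participate", and then "Seventy-six participants were randomly assigned to one of two conditions", 38 to each arm. The Abstract reports "Of the 355 patients screened, 61 participants were selected, randomly assigned to one of two conditions" "and completed the baseline assessment".

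**Losses after assignment.** The same Randomization section continues: "Before the start of the intervention, all participants were contacted by phone". At that stage "6 patients self-excluded from the study due to a lack of resources to attend the sessions". It does not say which arm the six were in. Intervention Implementation describes an experimental group of 32, in groups of 11, 12 and 9.

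**Timing of baseline.** Table 2 places randomisation and allocation at –t1 and lists t0 under the post-allocation heading.

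**Analysis.** Data Analysis says "All analyses are planned as intent-to-treat (ITT"). The primary model is an ANCOVA of the post-intervention DASS-21 adjusted for its baseline score. The text does not define the intent-to-treat set. The caption of Figure 1 has an asterisk for those included in it, but the figure itself is not visible. The section on attrition and missing data asks for data to be recorded as fully as possible on everyone recruited, in either arm. It plans multiple imputation when data are judged missing at random.

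**Awareness of allocation.** The Discussion says that "participants allocated to this condition were aware of their non-allocation to the intervention group" and accepts that this may affect self-report answers.

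**The concern.** The number randomised is the denominator on which an intent-to-treat claim rests. Here two explicit counts differ by 15. A reader of the Abstract alone would conclude that no one was lost between randomisation and baseline.

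The label is also at risk. Patients who left before T0 have neither the covariate nor the outcome of the primary model. If the analysis is confined to those who reached T0, it is an analysis of baseline completers. Only one arm was offered sessions, so withdrawal because sessions could not be attended may depend on the arm assigned. In that case the remaining groups need no longer be comparable by design, and the intent-to-treat label would promise more protection than the analysis gives.

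A related question is whether the DASS-21 at T0 was completed by people who already knew their arm. If it was, the covariate in every ANCOVA could itself have been affected by allocation.

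**Working it through.** **1. The plan's own sample size.** Inputs from Sample Size: SMD 0.75, alpha 0.05 (two-sided assumed; sidedness is not stated), power 80%, allocation 1:1.

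- Normal approximation: n per arm = 2 × (1.960 + 0.842)² / 0.75² = 27.9, so 28 per arm and 56 in total.
- Two-sample t-test: 28.9, so 29 per arm and 58 in total. The stated 58 is reproduced.
- ANCOVA with N – 3 degrees of freedom, taking 0.75 as the adjusted effect: power 80.1% at N = 58.

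**2. Participant flow, from the stated counts.**

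| Step | Arithmetic | Result |
|---|---|---|
| Left after screening | 355 – 279 | 76 |
| Randomised, by arm | 38 + 38 | 76 |
| Randomised but not among the 61 | 76 – 61 | 15 |
| As a share of those randomised | 15 / 76 | 19.7% |
| Left after the six with a stated reason | 76 – 6 | 70 |
| Losses with no reason in the visible text | 70 – 61 | 9 |
| Experimental group delivered | 11 + 12 + 9 | 32 |
| Experimental shortfall | 38 – 32 | 6 (6/38 = 15.8%) |

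The screening arithmetic supports 76 as the number randomised and 61 as the number with a baseline.

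**3. Split by arm (inferred).** If all 32 treated patients are among the 61, the control arm has 61 – 32 = 29. Its loss is then 38 – 29 = 9, or 9/38 = 23.7%. Fisher's exact test on 6/38 against 9/38 gives p = 0.57, so there is no clear imbalance in number. Similar counts do not show that the reasons were similar.

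**4. Power.** At SMD 0.75 by t-test, power is 89.7% with 76 patients and 82.1% with 61 (32 against 29). Both exceed the planned 80%.

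**5. Dilution scenario, not an estimate of bias.** Assume that all six were in the experimental arm, that they gained nothing, and that 0.75 is the effect among those who attended. The as-randomised effect would then be 0.75 × 32/38 = 0.63. The documents establish none of these assumptions.

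**The case against.** **The Abstract may only be condensed.** Its sentence strings three steps together, and 61 could be the number for whom all three hold. That is possible. But it offers no other figure for the number assigned, so it still misleads and needs correcting.

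**The intent-to-treat set may be all 76.** A reader might infer that the plan definitely drops 20% of randomised patients. The documents do not support that. No visible sentence says the set is the 61, and the figure that marks it is not shown, which is no fault of the plan. Imputation is planned, and the text does not exclude applying it to patients without T0. This stands, so the point about the label is conditional. Imputation would help little, however, for patients with no DASS-21 data at all, and the plan limits use of data when consent is withdrawn.

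**The losses may not be tied to allocation.** A reader might attribute all 15 to the arm assigned. A reason is given for only six, and their arm is not stated. The match with 38 – 32 = 6 suggests the experimental arm but does not prove it. For the other nine nothing is visible, and the missing figure may explain them. This stands too.

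**The baseline may not be contaminated.** The Discussion says controls knew their allocation, not that they knew before T0. Table 2 gives the order of randomisation and assessment, not the moment of disclosure. The telephone contact makes earlier disclosure plausible, no more.

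**Conclusion.** The contradiction is established: 76 randomised in the methods text against 61 in the Abstract, a gap of 15 patients (19.7%). Since Table 2 puts T0 after allocation, these 15 appear to be post-randomisation losses, six with a reason and nine without one in the visible text.

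The consequence for the analysis is conditional. If the baseline-adjusted ANCOVA is confined to the 61, it is a modified intent-to-treat analysis and the article's label is wrong. That it will be so confined is an inference from the Abstract and the model.

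Three stronger readings are not supported: that all the losses were caused by allocation, that the T0 covariate is known to be contaminated, and that the effect is overstated by a known amount. The figure of 0.63 illustrates one scenario only. Precision is not at stake, since power stays above 80% at 61. What is at stake is possible bias of unknown size and direction, and a label that may claim too much.

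**What to change.** 1. Correct the Abstract to 76 randomised (38 per arm) and 61 with a baseline assessment.
2. Report the 15 losses by arm and reason in the text, stating the arm of the six and the reasons for the other nine.
3. Define the analysis set in Data Analysis: either all 76 as intent-to-treat, or the 61 under the label modified intent-to-treat (randomised, with T0 data).
4. Where consent and retained data allow, add a sensitivity analysis of all 76 as randomised, with the assumptions for the 15 written down beforehand. Mark any dilution figure as a scenario.
5. State whether participants knew their allocation before completing T0. If they did, note that the baseline covariate may be affected.

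Replacing the T0 DASS-21 with the screening PHQ-9 as covariate is not recommended. The PHQ-9 is a depression measure, its range is cut by the exclusion of severe depression, and the article does not say the scores were kept for analysis.

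The cost is a few corrected sentences, one table of losses and one further analysis. The downside is a less favourable label if the set is the 61, and a sensitivity result that rests heavily on its assumptions, because these patients appear to have no DASS-21 data.

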### Sample Size

An *a priori* power analysis for this study was performed. In the absence of meta-analytic evidence, we have used data from Wynne et al. (25). Large reductions in mood symptoms were reported at follow-up for depression [*SMD* = 0.88 (0.557–1.21)], anxiety [*SMD* = 0.75 (0.423–1.068)], and stress [*SMD* = 1.1 (0.88–1.559)], even after adjustment for baseline values. Using the smallest of these effect estimates (anxiety), the inclusion of the baseline values as a covariate, an alpha of 0.05 and 80% power, we estimate that a total sample size of *n* = 58 would be required to power the primary analysis.

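### One named primary outcome, three DASS-21 subscales and a one-test sample size: the protocol does not fix which score, or how many of them, carries the efficacy claim

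*Protocol article*

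**What the plan says.** - **Aims of this Study** lists psychological distress as the one primary outcome.
- **Data Analysis** repeats the singular: "The primary outcome will be the psychological distress". A parenthesis then gives it as DASS-21 depression, anxiety and stress, "measured at 8 weeks (immediately post-intervention) between the two intervention groups and adjusting for baseline scores using ANCOVA".
- **Psychological distress** (under Primary Outcome) describes the instrument by its three symptom groups. Reliability is reported by subscale only: "The DASS-21 presented good internal consistencies for all subscales". No total score is defined. The scoring direction, "Higher scores indicate higher psychological distress", would fit either a subscale or a total.
- **Sample Size** quotes three separate SMDs from one earlier ACT trial in IBD: depression 0.88, anxiety 0.75, stress 1.1. It then plans on one of them: "Using the smallest of these effect estimates (anxiety), the inclusion of the baseline values as a covariate, an alpha of 0.05 and 80% power". The resulting total of 58 is what "would be required to power the primary analysis", in the singular.

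The article gives no rule for combining the three scores, no testing order and no division of alpha.

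**The concern.** An ANCOVA takes one dependent variable, so three scores mean three models unless they are summed. The subscale-by-subscale description and the use of separate subscale effects in the sample size make three tests the most natural reading. The sample size, however, allows for only one.

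The success rule determines what the stated alpha and power mean. If any subscale suffices, there are three chances of a false positive. If all are needed, there are three chances of missing a true effect. If a total is meant, the planning effect belongs to a different score from the one tested. The Discussion acknowledges that control participants knew their allocation and that this may influence their self-reports. Leaving the primary score open would therefore allow the most favourable subscale to be presented as the primary result.

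**Working it through.** **Inputs.** Alpha 0.05 and power 80%; SMDs of 0.88, 0.75 and 1.1 (Sample Size); 1:1 allocation (38 and 38, Randomization of Participants). The article gives no correlation between subscales, so r is an assumption and a range is shown. Tests are taken as two-sided.

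**1. The plan's own figure.** Normal approximation: n per arm = 2(1.960 + 0.842)² / 0.75² = 27.9, so 28 per arm and 56 in total. With the noncentral t and one covariate (N − 3 = 55 degrees of freedom), the noncentrality is 0.75 × √(58/4) = 2.856 and the critical value is 2.004. Power is 0.801 at N = 58 and 0.794 at N = 57. So 58 reproduces exactly as one test at 0.05, with no variance reduction credited to the baseline covariate.

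**2. If any one unadjusted subscale suffices.** With independent tests, 1 − 0.95³ = 0.143. For equicorrelated normal statistics with c = 1.96, the error is 1 − ∫ φ(u) [Φ((c − √r·u)/√(1 − r)) − Φ((−c − √r·u)/√(1 − r))]³ du:

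| r | 0 | 0.3 | 0.5 | 0.7 | 0.8 | 0.9 |
|---|---|---|---|---|---|---|
| Familywise error | 14.3% | 13.6% | 12.5% | 10.9% | 9.8% | 8.4% |

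**3. If all three must succeed.** Rejecting all three requires rejecting any one that is truly null, so the type I error cannot exceed 5%. With no effect on any subscale it is far lower: 0.3% at r = 0.5 and 0.9% at r = 0.7.

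Power at N = 58 for each subscale alone is 91% (0.88), 80% (0.75) and 98% (1.1). If independent, the joint power is 0.909 × 0.801 × 0.984 = 0.72. For correlated scores I used correlated normal statistics with the t critical value on 55 degrees of freedom:

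| r | 0 | 0.5 | 0.7 | 0.9 |
|---|---|---|---|---|
| Article's three SMDs | 72% | 76% | 78% | 80% |
| SMD 0.75 on every subscale | 52% | 62% | 66% | 73% |

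Joint power cannot exceed that of the weakest subscale (80%). With the article's SMDs it comes close to that only at very high correlation.

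**4. If the three tests are Bonferroni-adjusted.** At 0.05/3 = 0.0167 and N = 58, power is 65% for SMD 0.75, 81% for 0.88 and 95% for 1.1. Reaching 80% at SMD 0.75 needs 78 in total. These figures again credit nothing to the baseline covariate.

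**5. If a total score is tested once.** The error is 5%. Power cannot be computed, because the article gives no effect size for a total.

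**The case against.** **The text does not state three tests at 0.05.** A reader might infer that each subscale is tested at 0.05 and that the primary false-positive rate is therefore 11–14%. The documents do not support that. The only alpha appears in Sample Size, for a singular analysis. The assessment schedule and the longitudinal section list the DASS-21 as one entry, and the parenthesis in Data Analysis could simply name the instrument's components. A total score is not excluded, and no any-one-wins rule is written. The 11–14% range also needs correlations no higher than about 0.7; above that, the rate falls to 8–10%. This part of the objection stands, and it makes the error figures conditional.

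**Planning on the smallest effect fits an all-three rule.** It does, and such a rule does not inflate type I error. A reader might also infer power of only 62–66% under that rule, but this needs SMD 0.75 on every subscale. With the article's own values the shortfall is about 2–4 points at r = 0.5–0.7. This also stands.

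**The 65% Bonferroni power ignores baseline adjustment.** If 0.75 is on the unadjusted scale, a baseline–outcome correlation of 0.5 would raise it to about 79%. Sample Size says the reported reductions persisted after baseline adjustment, which leaves the scale unclear. So 65% holds only if there is no further precision gain.

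**Multiplicity can be left to the analysis plan.** The adjustment procedure can, and its absence here is not the point. Which score is primary and what counts as success belong in the protocol. Here the label, the listed scores and the sample size do not agree with one another. This part of the objection does not remove the concern.

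**Conclusion.** The concern holds as an unresolved primary endpoint: one outcome is named, three scores are listed, and the sample size is that of one test. That 58 equals a single 0.05 test at SMD 0.75 is exact.

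The consequences depend on the missing rule:

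- **Any one subscale, unadjusted:** error of roughly 8–14% for correlations from 0.9 down to 0.
- **All three:** error at or below 5%, with power about 76–78% at r = 0.5–0.7 using the article's SMDs, and 62–66% if every SMD is 0.75.
- **A single total:** error of 5%, with power unknown.

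The article does not establish that the trial's error rate is inflated. It leaves open a reading under which it would be. The stated 5% and 80% are shown to hold together only for a single test with a true SMD of 0.75, and the article does not say which score that test would use. The figures assume equal correlations between subscales, 29 per arm and no gain from the covariate.

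**What to change.** Choose one of the following and state it in Data Analysis and Sample Size.

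1. **Single primary score.** Name the DASS-21 total (all 21 items) at T1, the post-intervention assessment, as the only primary endpoint, tested once at two-sided 0.05 by baseline-adjusted ANCOVA. Report depression, anxiety and stress as secondary with Holm adjustment. State that the planning effect of 0.75 came from the anxiety subscale, so the 80% does not carry over directly to the total.
2. **Three co-primary subscales.** State either Holm adjustment with any subscale sufficing, or an explicit all-three rule. Restate the power at 58: about 65% for a subscale with SMD 0.75 at the Bonferroni level (Holm's first step), assuming no further covariate gain; or about 76–78% for all three with the article's SMDs at r = 0.5–0.7.

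No new data are needed. The cost of the first option is that an effect confined to one subscale is diluted in the total; the cost of the second is a less favourable power statement. Timing matters: recruitment ended in September 2019 and the article describes the assessments in the past tense. The choice should be documented as made before outcomes were examined by arm, or else disclosed as post hoc.
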